# Effect of IoT-based power cycling and quadriceps training on pain and function in patients with knee osteoarthritis: A randomized controlled trial protocol

**DOI:** 10.1097/MD.0000000000031841

**Published:** 2022-12-16

**Keywords:** exercise, knee osteoarthritis, power cycling, quadriceps training, tele-rehabilitation

## Abstract

**Methods::**

This study is a single-blind, 12-week parallel randomized controlled trial. Seventy-two participants aged ≥ 50 years with KOA will be randomized into either the power cycling group, the quadriceps group or the control group. The intervention will be performed three times per week during 12 weeks. Outcome measures will be assessed at baseline, and at 4, 8, and 12 weeks after allocation. The primary outcome will be self-reported pain, assessed with the Western Ontario and McMaster Universities Osteoarthritis Index (WOMAC) pain subscale. Secondary outcomes will include mitigation of knee pain, quality of life, improvement of functional physical performance, adherence of participants.

**Discussion::**

By summarizing the study’s strengths and limitations, this trial results may guide tele-rehabilitation of KOA in the community.

Trial registration: The study was registered in the clinical trial registry ChiCTR2200059255, 27/04/2022.

## 1. Introduction

Knee osteoarthritis (KOA) is a chronic disease involving the whole joint, including cartilage degeneration, bone remodeling, osteophyte formation, and synovial inflammation, which could lead to knee pain, stiffness, deformity and mobility impairment, reducing patients’ quality of life.^[1]^ A recent meta-analysis showed that the overall pooled estimate of symptomatic KOA prevalence in China is 14.6%.^[2]^ The prevalence of KOA grows in the aging and obese population in China.^[3]^ The disease not only imposes a significant disease burden on individuals, but also brings a serious economic burden to the national healthcare system.^[3,4]^

Exercise therapy, as core therapy for the non-surgical treatment of osteoarthritis, has been recommended by various guidelines.^[5–7]^ As a common form of aerobic exercise, power cycling uses the structure of existing fitness bikes, with which participants can get trained by overcoming frictional resistance, and achieving the purpose of exercise.^[8]^ There are some mechanisms of power cycling that relieves joint pain, such as remodeling of brain structure and function, compression of articular cartilage and reduction of lower limb weight-bearing.^[9–15]^ Therefore, it is often recommended for community-based rehabilitation of patients with KOA.^[16]^ However, its impact on quality of life is unclear, and the optimal exercise regimen is yet to be determined. Quadriceps training is a series of simple non-weight bearing open chain exercises to improve muscle strength and endurance (especially the main knee extensors), reduce stress on the knee joint, and improve the stability of the knee, thereby attenuating joint pain and improving function in patients with KOA.^[17,18]^ One study found that quadriceps training could alleviate pain in patients with KOA, but the training effect depends on the content of exercise training, the frequency and duration of intervention.^[19]^ There is currently no research to show which training strategy is best. Furthermore, at-home training, complex exercises could reduce the compliance of participants.^[20]^ Therefore, it is particularly important to choose quadriceps training that is reliable and easy to learn. Recent clinical trials have shown that both exercise regimens could significantly alleviate pain and improve joint function^[12,21,22]^; however, whether there is a significant difference in pain relief and function improvement between the two exercise types remains controversial.^[23]^

Despite knowing the benefits of rehabilitation and exercise therapy, it is not fully utilized in reality due to the demand of the time, geography and saturation of healthcare resources_._^[24]^ To break the geographical and time constraints of rehabilitation, tele-rehabilitation emerged in 1998,^[25]^ which can conduct health education, online assessment, exercise training and follow-up.^[26,27]^ With the development of modern technology, the platform of tele-rehabilitation has gradually transitioned from the telephone to the Internet and the emerging Internet of Things (IoT).^[28]^ IoT is a network based on and extending the Internet, with which the doctors can contact the patients and make adjustments to the therapy strategies individually.^[29]^ At the same time, IoT devices can collect patient data and store it in the cloud, enabling faster and more accurate data for sharing and analysis.^[30]^ A previous study conducted by our research team summarized the first IoT-based Chinese model for KOA rehabilitation in China, which verified the importance of IoT in rehabilitation.^[31]^ Supalak et al^[32]^ applied IoT technology to the treatment tracking of patients with KOA, through which the system could improve the accuracy of remote measurements, increase the follow-up rate after treatment and improve patients’ quality of life. However, the exercise therapy of KOA was not addressed in this study.

Although Internet-based rehabilitation is safe and feasible in clinical applications to relieve pain in patients with KOA,^[33–36]^ there are limited differences in support for the effects of these two types of exercise when combined with online exercise.

## 2. Methods

### 2.1. Aim

The aim of this randomized controlled trial is to directly compare the effects of two different exercise modalities, power cycling and quadriceps training combined with online guidance separately on KOA mitigation of pain in patients with KOA in a community, compared to the control group. We hypothesize that there will be a difference between these two rehabilitation strategies. Our secondary aim is to compare the effectiveness of two different exercise modalities on other outcomes, including quality of life, improvement of functional physical performance, adherence of participants.

### 2.2. Trial design

This trial is a three-armed, single-blinded and longitudinal 12-week parallel randomized controlled trial. The study protocol follows the Standard Protocol Items: Recommendations for Interventional Trials.^[37]^ Meanwhile, the report will be presented as the CONSORT guidelines.^[38]^ The flow chart of the clinical trial is shown in Figure 1.

**Figure 1. F1:**
[figure not shown]
Flow chart of the trial.

### 2.3. Study setting

This trial will be conducted in the community in Chengdu, Sichuan Province from December 2021 to December 2022.

### 2.4. Participants

We will recruit 72 patients with KOA. Participants’ inclusion criteria are: age ≥ 50 years with KOA, confirmed radiographically (Kellgren–Lawrence grade I–III), with 2021 Chinese Orthopedics Association guidelines for diagnosis and treatment of KOA clinical criteria^[39,40]^; knee pain (previous week) score of 3 to 6 on a numerical rating scale (NRS); able to use a smartphone to send messages and video calls; and able to communicate in Mandarin and understand Chinese characters.

Exclusion criteria are: having rheumatoid arthritis, gout or severe osteoporosis; preparing for knee replacement, other knee surgery in the next 6 months or knee surgery in the past 6 months; history of falls or fractures within the past 6 months; cancer; dementia or severe cognitive impairment; mental illness; diagnosis or suspicion of other conditions that limit exercise (e.g., stroke, heart failure, severe anemia, etc.); hypertension and diabetes not regularly medicated and monitored; other health problems that prevented them from participating in the project; and unable to sign informed consent.

### 2.5. Interventions

#### 2.5.1. Power cycling group.

The purposely designed WeChat applet “Huaxi Cloud Rehabilitation (HXCR)” enables the conduct of IoT-based rehabilitation programs, which mainly include education, and exercise programs according to the guidelines by Osteoarthritis Research Society International.^[7]^ The WeChat applet “Huaxi Cloud Rehabilitation” for Figure 2; The power cycling for Figure 3. During the trial, glucosamine hydrochloride is also required.^[40]^

**Figure 2. F2:**
[figure not shown]
The WeChat applet “Huaxi Cloud Rehabilitation”.

**Figure 3. F3:**
[figure not shown]
Instruction video for power cycling.

##### 2.5.1.1. Education.

By pushing knowledge about osteoarthritis disease and rehabilitation, participants will be able to understand their disease and the current status of their rehabilitation, build their confidence in rehabilitation and encourage them to actively participate in rehabilitation treatment. The doctors and physiotherapists will push educational materials related to KOA on the HXCR, including an introduction to the disease, rehabilitation treatment, healthy lifestyle (weight management, dietary management, etc.), etc. The same educational material is pushed to the participants 3 times a week, and the physiotherapist sends a relevant questionnaire to the participants at the end of each week to obtain the information received by the participants; the content is sent differently every week for a total of 12 sessions.

##### 2.5.1.2. Power cycling.

Power cycling will be performed 3 times a week for approximately 45 minutes for 12 weeks, and the exercise intensity was moderate. The intensity of exercise was measured by the rating of perceived exertion. When the rating of perceived exertion reaches 12 to 14(feeling some exertion during exercise), exercise is moderate.^[41]^ To avoid sports injuries, warm-up and cool-down activities are necessary; the time to reach exercise intensity is 30 minutes. The HXCR will send messages to the participant 3 times a week. If the participant does not complete the exercise on the same day, the message will continue to be sent to the participant on the next day, and if not completed on the next day, a message will be sent to alert the physiotherapist who will contact the participant by phone or video to check the status. Before the exercise, the physiotherapist will assess the participant and then push the exercise prescription to the participant’s applet based on the assessment results. Participants simply turn on the HXCR and scan the QR code on the power cycle to start exercising, no manual adjustments are required, and instant data (such as real-time speed, energy consumption, etc.) is displayed on the participant’s phone. A family member is required to accompany the participant during the exercise to ensure the safety of the participant. Each week, the physiotherapist will have a video link with the participant to see how he/she is doing and to record his/her response to symptoms. Exercise takes place at the community activity center power cycling parking.

### 2.6. Quadriceps group

Education and medication will be the same as the power cycling group.

#### 2.6.1. Quadriceps training.

Participants are required to perform progressive resistance strength training for 30 to 45 minutes 3 times per week for a total of 36 sessions. Physiotherapists pushed training videos to participants through the HXCR platform, and researchers guided participants through WeChat videos to ensure the quality of training. Participants need to be accompanied by their family members during each exercise session to ensure their safety. Each week, the physiotherapist will have a video link with the participant to see how he/she is doing, record his/her symptom response and decide on the amount of resistance to increase based on pain and fatigue; compliance will also be tested. According to the previous literature, we determined that there are 5 items of quadriceps muscle strength training: fixed range knee extension, sitting knee extension, sitting knee extension 30° maintenance, straight leg raise and sitting elastic band training.^[42]^

### 2.7. Control group

The control group will receive the same education and medication as the other two groups.

### 2.8. Outcome measures

Outcomes for the trial will be chosen based on Osteoarthritis Research Society International recommendations.^[43]^ Table 1 summarizes the primary and secondary outcome measures. Outcomes will be measured at baseline (T_0_) and at 4 (T_4_), 8 (T_8_) and 12 (T_12_) weeks after the allocation (Table 2).

**Table 1 T1:** Outcomes of this study.

Measurements	Metric of measurement	Method of measurement	Time point of primary interest
Primary outcomes			
Self-reported pain	0–20 (higher scores indicate more serious pain)	Western Ontario and McMaster Universities osteoarthritis index (WOMAC) – pain subscale	baseline, and 4, 8, and 12 wk after allocation
Secondary outcomes			
Self-reported pain	0–10 (higher scores indicate more serious pain)	Numerical pain rating scale (NRS)	baseline, and 4, 8, and 12 wk after allocation
Quality of life	Standardized scores for every section (higher scores indicate more better social participation)	The MOS item short from health survey (SF-36)	
Self-reported function and stiffness	0–76 (higher scores indicate more serious dysfunction)	WOMAC – physical function and stiffness subscale	
Functional performance	Seconds (shorter time indicates better function)	Timed up and go test	
Adherence	0–100% (Higher ratios indicate better adherence)	The ratio of the number of completed HXCR sessions to the total number of sessions	12 wk after allocation

HXCR = Huaxi Cloud Rehabilitation, NRS = numerical pain rating scale, SF-36 = The MOS item short from health survey, WOMAC = Western Ontario and McMaster Universities Osteoarthritis index.

**Table 2 T2:** The participant timeline.

Time point	Study period				
	Enrolment	Allocation	Post-allocation		
	−T_1_	0	T_4_	T_8_	T_12_
Enrolment					
Eligibility screening	×				
Informed consent	×				
Allocation		×			
Interventions					
Education					
Medication					
Exercise					
Assessment					
Sociodemographic data	×				
Personal and medical history	×				
IPAQ Short	×				
Primary outcome			×	×	×
Secondary outcomes			×	×	×

IPAQ Short = International Physical Activity Questionnaire.

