### 2.9. Sample size

The calculation is carried out according to the standard for the sample size of noninferiority trials and the unified standard for clinical trial reporting.^[38,56]^ Based on the degree of reduction in WOMAC pain scores was used as an index to assess the improvement in symptoms of KOA with each type of exercise. The literature was reviewed to obtain the means and standard deviations of changes in pain scores in the three groups of patients with KOA,^[42,57]^ The sample content estimate formula shows that, for a significance level of 0.05 and a yielding power of 90%,

$$\begin{array}{l} n=\varphi^{2}\left[\sum_{i=1}^{k}S_{i}^{2}/k\;\right]/\left[\sum_{i=1}^{k}{\left({\bar{X}}_{i}-\bar{X}\right)}^{2}/\left(k-1\right)\;\right]\; \end{array}$$

the sample size consists of 20 participants in each group. With a 20% dropout rate taken into account, each group needs 24 enrolled participants.

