### 2.14. Statistical analysis

Analyses will use an intention-to-treat analysis strategy. We will use one-way ANOVA to determine baseline comparability between groups for quantitative variable data. Baseline comparability between groups of categorical variable data will be determined using the chi-square test or other suitable nonparametric tests. Quantitative data will be expressed as the mean; if it follows normal distribution and homogeneity of variance, otherwise median is given. In statistical inference, if the data obeyed a normal distribution, and homogeneity of variance and satisfied spherical symmetry, repeated measures data analysis of variance was used; if the data did not obey a normal distribution or the variance was unequal, the Kruskal–Wallis H rank sum test was used for data analysis. SPSS (V21.0) will be used for data analyses. We considered *P* ≤ .05 to be statistically significant.

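### Neither Table 1 nor section 2.14 fixes one primary result for WOMAC pain: every visit is listed as primary, and no decisive model effect or fallback visit is named

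*Protocol article*

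**What the plan says.** Table 1 (section 2.8) has a column headed "Time point of primary interest". Its entry for WOMAC pain is "baseline, and 4, 8, and 12 wk after allocation". The secondary NRS pain score has the same entry, whereas adherence has a single time point, 12 weeks.

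Section 2.14 gives the analysis. If normality, equal variance and sphericity hold, "repeated measures data analysis of variance was used". If normality or equal variance fails, "the Kruskal–Wallis H rank sum test was used for data analysis". The decisive effect in the first case and the visit in the second are not named. The one error rule is that P is taken as "≤ .05 to be statistically significant".

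The abstract, the aim (2.1), the primary-outcome section (2.8.1) and the sample-size section (2.9) single out no visit either. Section 2.9 bases the calculation on the reduction in WOMAC pain without giving an end visit, and applies a three-group formula "for a significance level of 0.05 and a yielding power of 90" percent. From this it concludes that "the sample size consists of 20 participants in each group".

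**The concern.** A column meant to fix the primary time point has to single one out, or point to an analysis that combines the visits into one result. Here it repeats the assessment schedule, and the analysis section does not close the gap.

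A repeated-measures ANOVA yields a group test and a group×time test, and either could later be presented as the primary result. Kruskal–Wallis takes one value per patient, so the fallback must be run at a visit chosen later or at each visit in turn. The fallback is a real possibility: WOMAC pain is a bounded 0–20 score and the plan counts on 20 analysable patients per arm.

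At stake is whether the stated 5% describes the primary claim, and whether the 90% power belongs to an identifiable test. A choice made after the data are seen would also be open to suspicion, however well meant.

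**Working it through.** **Inputs from the article:** three arms; 20 analysable and 24 enrolled per arm; alpha 0.05; power 90%; post-baseline visits at weeks 4, 8 and 12 (2.8, 2.9, 2.14). Baseline cannot test a treatment effect, so the visit count for multiplicity is three, not four. **Assumed:** the correlation between visits, which is not given; 0 to 0.9 was used, equal for all pairs of visits.

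**1. The plan's own figure.** The 20 per arm cannot be recomputed, because the group means and SDs are cited but not printed. What it implies can be recovered. For a one-way ANOVA with 2 and 57 degrees of freedom and noncentrality 60 × f², 90% power at 0.05 gives f = 0.4716 (60 × 0.4716² ≈ 13.3). So the sample size serves one overall test, done once at 5%, on one change score per patient.

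**2. Repeated-measures ANOVA.** Each effect alone keeps its level: 4.8–5.2% in simulation. If either may count and the two are treated as independent, the error is 1 − 0.95² = 9.75%.

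**3. Kruskal–Wallis at each post-baseline visit.** Treated as independent, the error is 1 − 0.95³ = 14.3%.

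**4. Simulation.** 20,000 trials with no effect, 20 per arm, three post-baseline visits; chance of at least one P ≤ .05:

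| Visit correlation | Group or group×time | Kruskal–Wallis, any of 3 visits | 3 pairwise tests, one visit | 9 pairwise tests, 3 visits |
|---|---|---|---|---|
| 0 | 9.9% | 13.4% | 12.2% | 32.9% |
| 0.3 | 9.9% | 13.6% | 12.5% | 31.1% |
| 0.5 | 9.9% | 12.4% | 11.9% | 28.4% |
| 0.7 | 9.8% | 11.0% | 12.0% | 25.2% |
| 0.9 | 9.8% | 8.6% | 12.5% | 19.8% |

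The simulation error is about √(0.13 × 0.87 / 20,000) = 0.24 percentage points for the Kruskal–Wallis column, so 13.4% and 13.6% are not distinguishable. A separate run gave 28.8% to 22.4% for the nine tests at correlations 0.5 to 0.8. The first two result columns use tests that section 2.14 names. The last two do not.

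**5. Keeping all three visits as primary.** Bonferroni gives 0.05/3 = 0.0167 per visit. At f = 0.4716 and 90% power this needs 26 analysable per arm instead of 20. Enrolment becomes 26 × 1.2 = 31.2, so 32 (the multiplication that turns 20 into the plan's 24), or 26/0.8 = 32.5, so 33.

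**6. Overall test first, then pairwise.** With three arms, once the overall null is false at most one of the three pairwise nulls can still be true. Testing each pair at 5% after a significant overall test therefore holds the familywise error at 5%. Simulation of this rule at week 12 gave 5.0% with no effect anywhere and at most 4.8% with one arm different.

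**The case against.** The best defence is that the trial is described as longitudinal and the main analysis is a repeated-measures model. Such a model uses all visits in one analysis, baseline is an ordinary level of its time factor, and one effect tested once costs 5%. On this reading the Table 1 entry is loosely filled but harmless. That stands as far as it goes: repeated measurement does not itself inflate error, and listing baseline is not absurd. It does not remove the problem, because the effect is not named and the fallback cannot combine visits.

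A second defence is that multiplicity rules and the order of contrasts are commonly left to a statistical analysis plan, which is not shown. That also stands, and their absence is not the point here. The point is a statement this article does make: its table gives every visit as the one of primary interest. A later plan naming one visit would have to be reconciled with that table.

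A reader might go further and infer that any of nine visit-by-contrast results could be declared the primary finding, with a false-claim rate of 22–29%. The article does not support this. The outcome tests in section 2.14 and the formula in section 2.9 are overall three-group tests, and pairwise tests at each visit are not mentioned. Nor are the contrasts wholly unordered: section 2.1 hypothesizes a difference between the two exercise strategies, although it also refers to comparison with control.

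**Conclusion.** The point holds in a limited form. As written, the article does not identify one primary result for WOMAC pain. For the tests it names, the chance of a false primary claim when no arm differs is about 10% if either repeated-measures effect may count. It is about 9–14% if Kruskal–Wallis at any post-baseline visit may count. That is roughly two to nearly three times the stated 5%.

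These figures assume 20 analysable per arm and equal correlation between visits from 0 to 0.9; the Kruskal–Wallis figure depends on that correlation, while the repeated-measures figure hardly does. They also describe what the text permits, not what the investigators are shown to intend. With one effect or visit fixed in advance, the error is 5%. Unadjusted pairwise follow-up would add to it (about 12% at one visit), but only if it were done, and the text does not plan it explicitly.

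This should be fixed, but it does not invalidate the design.

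**What to change.** In Table 1, name one primary time point for WOMAC pain and make the other post-baseline visits secondary. Week 12 is a natural example, since the intervention ends then and adherence is judged then. Naming one repeated-measures effect as primary is an equally acceptable choice and stays closer to section 2.14; the text should then say whether baseline is a level of the time factor.

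Amend section 2.14 so that the model and the Kruskal–Wallis fallback target the same thing. With a named visit, both use the week-12 value or change. With a named effect, the fallback needs one stated summary per patient that corresponds to it. State that the overall three-arm effect is tested first at 5%, and the three pairwise contrasts at 5% each only if it is significant. Say in section 2.9 which visit the assumed changes refer to.

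The cost is one table cell and a few sentences. The 20 analysable per arm can stay, provided the literature values behind it fit the chosen visit or effect. The downside is that an effect seen only at week 4 or 8 can no longer be claimed as primary when week 12 is chosen.
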